## Abstract

**Background:**

Type 1 diabetes mellitus (T1DM) afflicts approximately 154,000 people under the age of 20 in the United States. Most people with T1DM are diagnosed at a young age, and parents have to take on the responsibility of T1DM management. Eventually, the child must begin to transition to self-management. Adolescents often struggle to take on responsibility for all the necessary tasks to successfully self-manage their T1DM. In fact, approximately three-quarters of adolescents are not achieving American Diabetes Association–recommended glycated hemoglobin (HbA_1c_) targets. This lack of adherence can lead to negative health outcomes.

**Objective:**

The goals of this interdisciplinary proposal are as follows: (1) to develop a unique and theory-driven technology using a mobile phone app to promote self-management behaviors for adolescents aged 10-15 years with T1DM and their parents and (2) to explore the feasibility and impact of the self-management mobile app.

**Methods:**

This study has two phases: app development and pilot testing. In the app development phase, the app will be conceptualized and a prototype will be tested. In Phase 2, the mobile app will undergo pilot testing to determine its feasibility and impact on diabetes self-management.

**Results:**

The pilot test was launched in September 2017. Data collection for the final pilot test is underway, and results are forthcoming.

**Conclusions:**

Adolescents with T1DM and their parents can have a difficult time managing the transition of diabetes care. It is hoped that this app can help. The focus groups and prototype testing have indicated promising outcomes of app use.

**Trial Registration:**

ClinicalTrials.gov NCT03436628; https://clinicaltrials.gov/ct2/show/NCT03436628 (Archived by WebCite at http://www.webcitation.org/72tHXTE2Z)

**International Registered Report Identifier (IRRID):**

RR1-10.2196/10803

## Introduction

Type 1 diabetes mellitus (T1DM) afflicts approximately 154,000 people under the age of 20 in the United States [1-3]. Most people with T1DM are diagnosed at a young age, and parents take on most of the responsibility for T1DM management. Optimal treatment requires the entire family to quickly learn about the disease and to oversee its management [4]. Starting in the early teen years, the child must begin to transition to self-management. During this transition, adolescents often struggle to take on responsibility for all the necessary tasks in order to successfully manage their T1DM [2,5]. Approximately three-quarters of adolescents are not achieving American Diabetes Association (ADA)–recommended glycated hemoglobin (HbA_1c_) targets. Achieving these targets requires consistent and dedicated management [6]. A lack of adherence to the prescribed treatment regimen can lead to negative health outcomes, such as the development of diabetic ketoacidosis, increased infections, and hospitalizations [7-9].

One reason for the lack of adherence is that as a child matures into an adolescent, communication between the child and his or her parent becomes increasingly difficult, and conflict often increases. There are data to suggest that improving communication between the adolescents and their parents facilitates a smoother transition to self-care and is one way to improve HbA_1c_ [10]. Mobile health (mHealth) technologies can also ease this transition by facilitating trust-building and improving family communication, relationships, and health outcomes. Nearly three-quarters of American teens (13-17 years old) have access to a smartphone [11]. Our hypothesis is that a mobile phone-based intervention that focuses on improving family communication will be effective in providing both the adolescents and their parents with real-time, tailored information about their diabetes and tools for communicating effectively**.**

Easing transition difficulties in an effort to increase positive health outcomes is imperative to the well-being of adolescents with T1DM and their families, and studies have shown that participants using mobile phone interventions had higher adherence rates and more participation than those that did not use the intervention [12]. Therefore, this study will develop a mobile app that addresses the difficulties of the adolescent transition to self-management and pilot test the app to determine its feasibility and impact on diabetes self-management. Below, we discuss the methodology for developing the app as well as the theoretical foundations guiding this development.

## Methods

### Study Design

This study has two phases that correspond with the study aims (Textbox 1): app development and pilot testing. In the app development phase, the app will be conceptualized and a prototype will be tested. In Phase 2, the mobile app will undergo pilot testing to determine its feasibility and impact on diabetes self-management. We did not utilize a control group because this is a feasibility study [13].

### Theoretical Foundation

The social cognitive theory will inform the development of the intervention. The use of this theory to guide interventions has demonstrated success in changing behaviors around disease management [14-17]. The social cognitive theory posits that a change in an individual’s environmental, personal, or behavioral factors will impact the other two factors [18-21]; thus, the relationship among these factors is reciprocal. The self-management mobile app is being developed to lead to changes in each of the three factors. For example, to change the adolescents’ environmental factors, we will provide social support through a forum feature [22-24]. We believe that receiving messages from their parents via the self-management mobile app will also be a part of the environmental change [25-28]. Personal factors will be modified by prompts sent to the adolescents to set small and achievable daily goals, blood sugar reminders, and educational tips about living with T1DM to improve the adolescents’ self-efficacy [29-34]. Behavioral change will result from reinforcement through reminders and awarding points for achieving goals and entering data. The points encourage use (behavior), which we predict will improve adolescent adherence [35]. As a result of all of these factors, children will have an improved HbA_1c_, a higher quality of life, and reduced conflict with their parents, which we believe will reinforce the use of the self-management mobile app, strengthening the links. Figure 1 shows the theoretical model for the intervention.

Specific aims.
**Phase 1**

*Specific Aim 1: Develop a type 1 diabetes self-management mobile phone app intervention for parents and adolescents*
Objective 1: Develop the self-management mobile app and finalize contentObjective 2: Prototype testing
**Phase 2**

*Specific Aim 2: Conduct pilot testing of the self-management mobile app to determine its feasibility and impact on diabetes self-management*
H1 (primary outcomes): Measures of app usage will be associated with increased adherence to self-management and lower glycosylated hemoglobin.H2 (secondary outcomes): Measures of app usage will be associated with increased quality of life, self-efficacy, and social support and decreased conflict between the adolescents and their parents.

**Figure 1 figure1:**
[figure not shown]
Theoretical model. HbA_1c_: glycated hemoglobin.

### Phase 1: Technical App Development

The technical app development (Phase 1) will take place over a 9-month period. This process will be monitored through set goals, and progress will be measured by achieving two objectives of developing the self-management mobile app and finalizing content. To complete these objectives, content development will be completed based on several sources, including *Understanding Diabetes* [36] and other literature from the ADA, in conjunction with an expert panel who will also advise on the project during implementation. This panel includes a pediatric endocrinologist, a pediatric diabetes nurse practitioner, a college student with T1DM, and a parent of an adolescent with T1DM (not part of the study).

Based upon best practices in app design principles [37], we will also conduct focus groups with participants recruited from our target population. We will invite 6 adolescents and their parents for concept-testing focus groups. We will present the app concept and mock screenshots to the participants and solicit feedback with regard to the app’s look and feel, message wording, and what would help the adolescents to log their values. The data from the focus groups will inform message content refinement, the timing of the messages, their appropriateness, and the ease of logging information. This information will inform the app’s technical development. The technology development (app interfaces, Web portal, and servers) will be informed by the focus groups, concept testing, and best practices literature. We have 10 benchmarks with deadlines for app development (Table 1).

Once the prototype is developed, the objective 2 will be met by prototype testing of the app. We will recruit 10 family dyads (each dyad includes a teen and his or her parent, n=20) to use the self-management mobile app prototype over a 4-week period. We will conduct usability interviews, measuring perceptions and satisfaction with the app. Additionally, server information will be used to quantify learning time, the efficiency of use, engagement, and user errors. All of the problems and issues identified in the usability interviews will inform app development and refinement.

#### The Mobile App

##### App Functionalities

The self-management mobile app will be an intervention mechanism to encourage adolescents aged 10 to 15 years to self-manage their diabetes by recording their values while allowing their parents seamless and unobtrusive access to the same blood glucose (BG) values, carbohydrate intake, and physical activity data, which will be time-stamped, encrypted, and sent to a remote server for storage.

**Table 1 table1:** App development benchmarks.

Step	Time (in days)
Server management	13
User management	13
Server side logic	12
Data integration	13
Push logic	6
Versioning	12
Cache logic	6
Synchronization	8
Wireframe development	8
User interface design & development	33

The parent users will have a separate log-in and will be able to review their child's history of BG values, carbohydrate intake, and physical activity from their own phone to help their child make decisions about managing their diabetes. Parents may also send messages via the app to their child. However, the parent can still communicate outside of the app, and we will ask about this communication in the poststudy interviews.

Along with customizable test reminders and BG ranges, the app will also have an educational component and a moderated forum for the adolescents and the parents (separate forums) to post and discuss questions and comments to peers. The adolescents will be incentivized through the use of points accumulated based on usage. These points can be used by the adolescents to purchase accessories for a superhero avatar. As this is a feasibility study, we will have the adolescents manually input their BG readings into the app. While this may seem cumbersome, most meters and pumps do not have the ability to automatically send data through Bluetooth. Once we can determine the feasibility and other design requirements through this pilot, we will develop the app to be Bluetooth-enabled. The participants and their parents are responsible for notifying their medical providers regarding any issues with their diabetes. Our app will not cause an actual health concern, as it is just a monitoring and communication device.

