#### Study Procedures.

During the study, there will be 4 contact points with the participants: the enrollment or baseline data collection visit (Visit 1), a midpoint review (Visit 2, 3 months after Visit 1), an end-of-study visit (Visit 3, 6 months after Visit 1), and a follow-up visit 3 months after app usage has stopped (Visit 4). Visit 1 (month 0) will be scheduled during the screening process. At Visit 1, a member of the research team will review and obtain informed consent (parent) and assent (adolescent) from the participants. The participants will then complete the baseline surveys to measure self-efficacy, quality of life, and social support and conflict; the laboratory will test the teens’ HbA_1c_, and we will download data from their glucometer or pump. If a participant does not have a mobile device that can download and operate the app, the research team will provide the participant with a device and data plan for the duration of the study. The researcher will demonstrate how to use the technology and have the participants use each of the functions. At Visit 2 (month 3), a research team member will test the adolescents’ HbA_1c_ and download data from their glucometer or pump. The participants will also complete the survey at the midpoint. The midpoint data will be used to demonstrate whether any change at 6 months is part of an increasing trend, a plateau, or a waning trend. At Visit 3 (month 6), the participants will complete the survey and participate in interviews. Additionally, the adolescents’ HbA_1c_ will be tested, and the meter or pump readings will be collected. Finally, any participant that has borrowed any equipment will need to return it at this time. Qualitative methods will also be used to better examine perceptions and intentions, whether participants were light users, or why participants dropped out of the study [39]. After Visit 3, the participants will not use the app for 3 months. At Visit 4 (month 9), all the participants will complete the survey. The researchers will test the adolescents’ HbA_1c_ and download data from their glucometer or pump.

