#### Outcome Measures

Specifically, the aim 2 seeks to determine the feasibility and impact on diabetes of the self-management mobile app among the adolescents and their parents. Demographic information will also be collected including current age, age at diagnosis, race, gender, parental status (ie, mom, dad, stepdad, etc), and method of diabetes treatment (eg, pump).

Hypothesis 1 seeks to demonstrate that adherence to self-management correlates with mobile app usage and a decrease in HbA_1c_. HbA_1c_ data will be collected through the hospital laboratory system. The patient will be provided with a laboratory slip to obtain the baseline HbA_1c_ value. The patient will be instructed to obtain the lab results within 1 week. Once the results are obtained, they will be faxed to the principal investigator via a secure fax line. Adherence will be measured in two ways. First, the participants will complete the Diabetes Behavior Rating Scale [40]. Second, we will use data from the server to determine if they are monitoring blood sugar on schedule and what mechanisms of the app helped the adolescents follow the medical recommendations. For example, we will use time-stamped log-ins, number of sections the user visited, number of individual logs, communication through the app, educational information accessed, and duration of use per log-on.

Hypothesis 2 states that through use of the app, the participants’ self-efficacy [29,41,42], quality of life [43-45], and perceptions of social support [46-48] will improve, and conflict [49] between the child and parent will be reduced from baseline to 3 months. These secondary outcomes are key in helping the adolescents maintain adherence and a normal HbA_1c_ [50-52] and will be measured through surveys. The survey instruments, the participants who will complete them, and reliability for each measure can be found in Table 2.

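### Glucose values are typed in by the teen and rewarded with points, but the meter and pump downloads that could verify them have no stated use

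*Protocol article*

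**What the plan says.** All references are to the protocol article.

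- **Entry.** App Functionalities states that "we will have the adolescents manually input their BG readings into the app". It gives the reason (most devices cannot transmit by Bluetooth) and defers automatic transfer until after this pilot.
- **Reward.** Theoretical Foundation describes reinforcement that includes "awarding points for achieving goals and entering data". App Functionalities adds: "The adolescents will be incentivized through the use of points accumulated based on usage". The points buy accessories for an avatar. No accuracy condition is mentioned.
- **Use by parents.** Parents review the history "from their own phone to help their child make decisions about managing their diabetes".
- **Device record.** At Visit 1, Study Procedures says "we will download data from their glucometer or pump". The same is planned at Visits 2 and 4, and at Visit 3 "the meter or pump readings will be collected".
- **Measurement.** Outcome Measures says "Adherence will be measured in two ways": by the Diabetes Behavior Rating Scale and by app server data. The server data are to show whether glucose checks are done on time. Six kinds of server measure are listed as examples, one of which is the count of log entries.
- **Analysis and feasibility.** Analysis and Statistical Power does not mention the downloads. Its primary foci are effect size, app feasibility, practicality of data collection and ability to implement.

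**The concern.** The server holds what the adolescent chose to type, while the meter or pump holds what was measured. The two can differ in three ways: a reading taken but not entered, a value entered with no reading behind it, and a value entered differently from the reading. Rewarding entry gives some reason to expect the second. The Introduction's account of rising parent-child conflict at this age gives some reason to expect the first and third.

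Two conclusions are at stake. One is feasibility: whether hand-entered logs are good enough is a natural question for a pilot whose stated next step is to replace hand entry with Bluetooth. The other is measurement: a server-based judgement of on-schedule monitoring, and a count of log entries used as an app-usage measure, both depend on the correspondence between typing and testing, which the plan as described leaves unexamined.

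**Working it through.** The article gives no figure on agreement between app and device, so there is none to reproduce. The check compares sections and then asks what the planned sample could show.

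**1. Which source answers which question**

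| Question | Source assigned in the article | Device record available? |
|---|---|---|
| Is glucose checked on time? | App server data (Outcome Measures) | Yes, all four visits (Study Procedures) |
| How much is the app used? | Server data, including log count (Outcome Measures) | Could verify log entries |
| Is manual entry feasible? | Primary foci, with no accuracy or completeness item (Analysis and Statistical Power) | Yes, but not mentioned |

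**2. How the server-based judgement classifies a scheduled check**

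| | Entered in app | Not entered |
|---|---|---|
| Tested on device | counted as monitored (correct) | counted as not monitored (wrong) |
| Not tested | counted as monitored (wrong) | counted as not monitored (correct) |

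The two wrong cells push in opposite directions, so the net bias in the adherence measure cannot be signed from the documents. Only the device record separates the right cells from the wrong ones.

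**3. Would the planned data screening find the errors?** Analysis and Statistical Power plans histograms and box-plots of each measure at each time point. These can flag an implausible value. They cannot reveal a reading that was never entered, or an invented one of plausible size.

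**4. Could the planned sample measure the problem?** Inputs: n = 70 dyads planned, and n = 56 after the 20% attrition that the article allows. The share p of dyads with discordant logs is an assumption, shown over a range.

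Chance of at least one discordant dyad = 1 − (1 − p)^n:

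| p (assumed) | n = 70 | n = 56 |
|---|---|---|
| 2% | 0.757 | 0.677 |
| 5% | 0.972 | 0.943 |
| 10% | 0.999 | 0.997 |
| 20% | 1.000 | 1.000 |

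Worked for p = 5%: 1 − 0.95^70 = 0.972 and 1 − 0.95^56 = 0.943.

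Precision (exact Clopper-Pearson 95% interval): 14 of 70 (20%) gives 11.4% to 31.3%, and 11 of 56 (19.6%) gives 10.2% to 32.4%. That is informative at pilot scale without additional participants.

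**The case against.** **The article is a condensed account.** Matching rules and tolerances belong in a full protocol or analysis plan, which is not shown. This stands in part: one can say only that no comparison is described, not that none is planned. But the article does specify the measures. It names the source for on-schedule monitoring and chooses the server over the device record, and that choice can be reviewed as written.

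**Manual entry is disclosed and reasoned.** This stands. The point is not that entry is manual, but that the pilot as described does not test how well it works.

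**The log count is one of six server measures, and HbA1c is a laboratory value.** This stands. Entries made for points and unrelated to HbA1c would add noise and tend to weaken that association, not create one. Inflated associations cannot be claimed as the expected result.

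Stronger readings that a reader might infer, and why the documents do not support them:

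- *The app is an unsafe information channel.* Nothing shows that parents check less or are misled. App Functionalities notes that parents can communicate outside the app and makes families responsible for notifying providers of problems. Study Setting schedules clinic visits every 3 months.
- *Errors would be undetectable.* The downloads are collected, so a comparison remains possible. Only a stated analysis is missing.
- *The article misdescribes what parents see.* It speaks of "allowing their parents seamless and unobtrusive access to the same blood glucose (BG) values", which naturally means the values the adolescent recorded. That is accurate and needs no correction.
- *An invented value earns the same points as a real one.* The scoring rule is not given. The article only mentions no accuracy condition.
- *A count of wrong readings can be projected.* That would need an assumed testing frequency, an assumed error rate and a period of app use. The article gives the last as 3 months under Phase 2: Intervention Study Methods but as 6 months under Study Procedures.

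**Conclusion.** The concern holds in a limited form. The article assigns the judgement of on-schedule monitoring to hand-entered, rewarded app data and gives the device downloads no stated role. As described, the pilot could therefore conclude that manual entry is feasible without knowing whether the logs are complete and accurate, and its log-based measures could reflect entry behaviour rather than testing.

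The size and direction of any resulting error are unknown, because the documents contain no concordance figure. The detection probabilities show only that the planned sample is large enough to look, and they rest on assumed discordance rates. The conclusion assumes that no comparison is specified in the full protocol; if one is, it should be stated. This is worth correcting but not fatal to the pilot.

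**What to change.** 1. **Outcome Measures.** State the use of the downloads, and judge on-schedule monitoring from the device record.
2. **Analysis and Statistical Power, analysis text.** At Visits 2 and 3, match time-stamped app entries to downloaded readings within a time and value tolerance fixed before the data are seen. An entry outside the value tolerance counts as unmatched.
3. **Analysis and Statistical Power, primary foci.** Add as feasibility outcomes, per adolescent: (i) the share of device readings logged in the app; (ii) the share of app entries with no device match; (iii) the share of out-of-range device readings not logged, with the range defined in advance by the trial team.
4. **Sensitivity analysis.** Repeat the log-count analyses using device-matched entries only.

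The matching window depends on how long the app is used, so the 3-month and 6-month statements must be reconciled first.

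**Cost.** Both data sets are already collected, so no visits, procedures or participants are added. The work is linkage and a tolerance rule for clock differences between meter and phone. Some devices hold incomplete history, so the shares should be computed only over the period that each download covers. A second meter that is not downloaded would also leave genuine entries unmatched, so an unmatched entry should not be reported as a false one.
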